## Abstract

**Background:**

Cannabis is the most-frequently used illicit drug in Europe. Over the last few years in Spain, treatment demand has increased, yet most cannabis users do not seek treatment despite the related problems. A web-based self-help tool, like CANreduce 2.0, could help these users to control their consumption.

**Methods:**

This study protocol describes a three-arm randomized controlled trial (RCT) comparing the effectiveness of three approaches, in terms of reducing cannabis use among problematic cannabis users, the first two treatment arms including the Spanish version of CANreduce 2.0 (an adherence-focused, guidance-enhanced, web-based self-help tool) (1) with and (2) without psychological support; and the third group (3) treatment as usual (TAU). Study hypotheses will be tested concerning the primary outcome: change in the number of days of cannabis use over the previous week, comparing assessments at 6 weeks and 3 and 6 months follow-up between groups and against baseline. Secondary outcomes related to cannabis use will be tested similarly. Mental disorders will be explored as predictors of adherence and outcomes. Analyses will be performed on an intention-to-treat basis, then verified by complete case analyses.

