For the current study, CANreduce 2.0 (an adherence-focused, guidance-enhanced, web-based self-help tool) [26] was translated into Spanish (CANreduce-SP) and its effectiveness with versus without psychological support compared, in terms of reducing cannabis use among problematic users. Adding psychological support (the option for program users to contact an e-coach to resolve doubts or any concerns they have regarding the program or process) is expected to optimize both adherence to and the effectiveness of the program. Previous studies have identified low demand for this type of support, but better results with similar support options, like chat sessions with a counsellor [24].

Study hypotheses will be tested concerning the main outcome: reduction in the number of days of cannabis use over the prior week, comparing assessments at baseline versus 6-week, 3-month, and 6-month follow-up. A priori study hypotheses are:

The CANreduce-SP program with psychological support (study arm 1) will be more effective than CANreduce-SP with no psychological support (study arm 2) at reducing cannabis use.The CANreduce-SP program with psychological support (study arm 1) will be more effective than treatment as usual (TAU, study arm 3) at reducing cannabis use.The CANreduce-SP program without psychological support (study arm 2) will be more effective than TAU (study arm 3) at reducing cannabis use.Participants in study arm 1 will demonstrate better adherence than participants in study arm 2 over the 6-week intervention.

Secondary cannabis-related outcomes will be tested similarly, and frequently co-occurring mental disorders explored as predictors of adherence and outcomes.

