## Methods/design

The Spanish version of the adherence-focused, guidance-enhanced, web-based self-help program CANreduce 2.0 (CANreduce-SP) will be evaluated within a three-arm RCT, in which the effectiveness of CANreduce-SP with psychological support and CANreduce-SP without psychological support will be compared against each other and against treatment-as-usual (TAU) at reducing cannabis use in problematic users. Given that the study will only be partially single-blinded, the two active intervention arms will be neutrally described to subjects assigned to those arms to prevent participants from preferring one over the other. However, participants assigned to TAU will immediately be made aware of their group. As for study personnel, though any who directly provided support to program users cannot feasibly be blinded to subjects’ group assignments, all other study personnel (e.g. those involved in data collection, editing and analysis) will be. Co-occurring mental health symptoms will be screened with the rest of the primary and secondary outcomes during the baseline assessment (*t*_0_) to ensure that all potential participants meet study criteria and are eligible to be randomized and allocated to one of the three study conditions. Further assessments will take place 6 weeks after baseline, which is also the time when participants will have completed the 6-week program (*t*_1_), as well as at 3 months (*t*_2_), and 6 months (*t*_3_) follow-up (Fig. 1). Having 6 months of follow-up will allow us to examine the durability of any changes achieved with either of the two active interventions (study arms 1 and 2). For ethical reasons, we have elected not to ask study participants in the TAU group to wait a full 6 months for their final follow-up. Instead, we will grant them access to the intervention group without psychological support (study arm 2) 18 weeks after baseline—6 weeks after their 3-month evaluation (*t*_2_)—with the intention of assessing any response to the program they might have had at the 6-month follow-up assessment (t_3_). In this way, they will provide the study with a further, cross-over comparison.

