### Randomization and trial flow

Once participants have completed their baseline assessment (*t*_0_), they will be randomized by a computer algorithm in a 1:1:1 ratio into one of three parallel groups and will be registered automatically in the background database. Participants’ internet protocol (IP) address will be monitored to prevent multiple registrations from one user attempting to have more than a single account or be allocated to a different group than originally assigned. Participants assigned to the control condition (TAU/study arm 3) will be remitted to a list with the treatment centres nearest their postal code. After 3 months in TAU, participants will gain access to CANreduce-SP without psychological support. The four assessment points of the study are depicted in Fig. 1. All subjects will be asked about their potential for using some different treatment during their participation in the study. A reminder e-mail will be sent before each assessment. It will contain information about the value of their answers, the estimated length of the questionnaire (in time to complete), and compensation for each evaluation to enhance the response rate. The same e-mail will be sent if there is no answer within 2 days and again after 4 days. One week after the last e-mail, participants will be contacted by phone and will be offered the option of completing the follow-up questionnaire verbally with an interviewer. Participants who drop out will be asked to answer a few questions pertaining to the two the primary outcomes and why they have decided not to continue in the study. Inactivity will not be considered a dropout criterion, due to the breaks that participants of web-based interventions commonly take. It is expected that some of these users will re-join the program later. A participant’s active withdrawal from the study will be the only dropout criteria. If possible, all data already gathered from these participants will be analysed. Figure 1 depicts the flow of subjects through the study.

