#### Control condition

The control condition will be treatment as usual (TAU). Participants will be informed about this group's relevance, their path in the study (Fig. 1) and the link to the Plan Nacional Sobre Drogas (National Drug Plan) web page to find information about the drug treatment centre nearest their place of residence. During the 3-month assessment at (*t*_2_), as with the two active intervention groups (study arms 1 and 2), TAU group participants will be asked if they have used other treatments during their study participation and what they were. Then, they will be reallocated into intervention group 2 (study arm 2) to access all the CANreduce resources, except psychological support, and will have their last assessment (t_3_) after this 6-week program.

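### At 6 months the planned comparisons with TAU are comparisons with delayed CANreduce-SP, so they do not test hypotheses 2 and 3

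*Protocol article*

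**What the plan says.** The Methods paragraph of the abstract says the hypotheses will be tested on days of cannabis use in the previous week by "comparing assessments at 6 weeks and 3 and 6 months follow-up between groups and against baseline".

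The Background introduces the a priori hypotheses with "comparing assessments at baseline versus 6-week, 3-month, and 6-month follow-up". Hypothesis 2 is that arm 1 "will be more effective than treatment as usual (TAU, study arm 3) at reducing cannabis use", and hypothesis 3 is that arm 2 "will be more effective than TAU (study arm 3) at reducing cannabis use". Neither is limited to particular time points.

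Three sections describe when arm 3 stops being TAU:

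- Methods/design: for ethical reasons, "we will grant them access to the intervention group without psychological support (study arm 2) 18 weeks after baseline", which it equates to six weeks after the 3-month assessment (t2). The stated aim is to see at t3 how these participants responded. It adds: "In this way, they will provide the study with a further, cross-over comparison".
- Randomization and trial flow: "After 3 months in TAU, participants will gain access to CANreduce-SP without psychological support".
- Control condition, after describing the questions asked at t2: "Then, they will be reallocated into intervention group 2 (study arm 2) to access all the CANreduce resources, except psychological support". It places their last assessment (t3) after the 6-week course.

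Data analysis specifies intention-to-treat analysis, with a linear regression of the outcome on allocated group and baseline covariates. It names no time point and does not limit the contrasts that involve arm 3.

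**The concern.** Hypotheses 2 and 3 are claims of superiority over TAU. The text places a between-group test of the primary outcome at a time when, by design, the TAU arm has been given the programme under test. Followed literally, two of the three efficacy hypotheses would be tested at one of three time points against a control group that has been offered the intervention.

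The risk lies in interpretation. A smaller or absent difference at t3 could be read as an effect that faded when the controls had simply received the programme. The cross-over comparison mentioned in Methods/design does not fill the gap. Only arm 3 switches, and between t2 and t3 no arm remains without the programme. Change in arm 3 over that interval therefore cannot be separated from time trends or regression to the mean.

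**Working it through.** **1. The protocol's own figure.** Inputs from Sample size calculation: d = 0.40, two-sided alpha 0.05, power 80%, t-test. The normal approximation n = 2(1.960 + 0.842)² / 0.40² = 98.1 rounds up to 99 per group. The exact t-test needs 99.08, so 100 per group, with power 80.4% at n = 100. The stated 100 per group is reproduced.

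**2. Timing.** Six months is about 26 weeks.

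- Access at 18 weeks (Methods/design): 18 + 6 = week 24.
- Access at 3 months (Randomization and trial flow; Control condition): 12 or 13 weeks, depending on how a month is counted, + 6 = week 18 or 19.

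Under either timing the scheduled course ends before t3. The primary outcome covers the seven days before assessment (Measurements), so at t3 the whole window lies after arm 3 gained access.

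**3. What each t3 contrast estimates.** Relative to no programme, let P be the effect of immediate access still present at t3, S the added effect of psychological support, and D the effect of delayed access in arm 3.

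- Arm 2 versus arm 3 estimates P − D. Hypothesis 3 concerns P.
- Arm 1 versus arm 3 estimates P + S − D. Hypothesis 2 concerns P + S.
- Arm 1 versus arm 2 estimates S, as hypothesis 1 requires.

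If D = P, the first contrast is zero although the programme works, and the second is S. If P has faded and D is recent, D can exceed P and the first contrast changes sign. At t1 D = 0. At t2 D = 0 as well, provided access follows that assessment.

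**4. Size, as an illustration.** Write f = D/P for the share of the effect that arm 3 has gained by t3. The protocol gives no value, so f is an assumption and is varied over its range. Residual d = 0.40 × (1 − f). Power is from the exact two-sided t-test with noncentrality d√(n/2) and 2n − 2 degrees of freedom. At n = 100 and f = 0.50, for example, the noncentrality is 0.20 × √50 = 1.41.

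| f (assumed) | Residual d | 75 per arm | 100 per arm | 150 per arm |
|---|---|---|---|---|
| 0 | 0.40 | 68% | 80% | 93% |
| 0.25 | 0.30 | 45% | 56% | 74% |
| 0.50 | 0.20 | 23% | 29% | 41% |
| 0.75 | 0.10 | 9% | 11% | 14% |
| 1 | 0 | 5% | 5% | 5% |

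The middle column uses the protocol's target of 100 per group. The outer columns are the 150 per group to be randomised (450/3), with 50% attrition (75) and with none (150).

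**The case against.** The delayed access is disclosed, has an ethical reason and is given its own purpose. Methods/design calls the arm 3 data at t3 a further comparison, which suggests something additional to the tests of hypotheses 2 and 3. The Background wording can be read as change from baseline only. A between-group test at 6 months also validly covers arm 1 versus arm 2. Which time point tests which hypothesis is often settled in the full protocol or SAP, and neither is shown. All of this is fair, and the delayed access itself is not criticised here. But an additional comparison does not replace the listed ones. The abstract positively names 6 months as a between-group time point without exempting TAU, and Data analysis does not correct it.

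A reader might infer more than the documents support:

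- *That the t3 contrast with arm 3 is biased towards no difference.* By intention to treat it is a valid randomised comparison of immediate with delayed access, which is a different question. Its direction is not assured, and any effect of support remains in arm 1 versus arm 3.
- *That durability can no longer be studied.* Methods/design claims durability only for changes within arms 1 and 2. Late access in arm 3 does not touch that.
- *That former TAU participants will be pooled into arm 2.* The word for reallocation in Control condition might suggest it, but no section plans it, and intention-to-treat analysis by allocated group excludes it.
- *That the power figures forecast the loss.* They depend on uptake and response in arm 3, which the protocol does not give, and the Limitations section expects low adherence in web-based studies.

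**Conclusion.** The point holds for the 6-month contrasts with arm 3, which are not comparisons with TAU and do not test hypotheses 2 and 3. That conclusion rests only on the sequence of events, and it is the same under each stated access time.

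The size is conditional. If the programme works and its effect persists, the t3 difference will tend to shrink. At 100 analysed per arm, power falls from 80% to between 56% and 5% as the assumed share gained by arm 3 rises from 25% to 100%.

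It would go too far to conclude that hypotheses 2 and 3 are untestable. They remain testable at 6 weeks and, with access after t2, at 3 months. Hypotheses 1 and 4 and within-arm durability in arms 1 and 2 are unaffected.

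**What to change.** - State that hypotheses 2 and 3 are tested at t1 and t2 only, and that t2 is the last randomised comparison against TAU. Carry this through the abstract, the Background hypotheses and Data analysis.
- At t3, keep arm 1 versus arm 2 as the confirmatory between-arm contrast.
- Report arm 3 at t3 either as immediate versus delayed access or as uncontrolled within-group change after delayed access. Do not present it as a comparison with TAU. Say explicitly that arm 3 is analysed as randomised.
- Reconcile when TAU participants gain access: Methods/design gives 18 weeks, Randomization and trial flow gives after 3 months, and Control condition has it follow the t2 assessment.

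The cost is wording. Sample size, data collection and the t1 and t2 analyses do not change. The trial gives up a 6-month claim against TAU, which the design cannot support in any case.

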**Discussion:**

This study will test how effective the Spanish version of CANreduce 2.0 (CANreduce-SP) is at reducing both the frequency and quantity of cannabis use in problematic users and whether adding psychological support increases its effectiveness.

**Trial registration:**

This trial is registered with the Clinical Trials Protocol Registration and Results System (PRS) number: NCT04517474. Registered 18 August 2020, (Archived by archive.is https://archive.is/N1Y64). The project commenced in November 2020 and recruitment is anticipated to end by November 2022.

## Background

Cannabis is currently the third most frequently consumed drug in the world, after alcohol and tobacco. According to the latest report by the United Nations Office on Drugs and Crime, approximately 192 million people between 15 and 64 years old have used cannabis in the past year [1]. An increasing number of jurisdictions worldwide have legalized or are about to legalize cannabis. To date, however, it is hard to assess the influence these changes might have in many areas of interest, like the demand for treatment of cannabis use disorder (CUD), the changes’ impact on public health, and their legal ramifications [2, 3]. Nevertheless, it is noteworthy that both the number of people who use cannabis frequently and the overall frequency of the drug’s use have increased in all these jurisdictions since legalization, and more potent cannabis products are now more readily available in these markets [4, 5].

In Europe, the European Monitoring Center on Drugs and Drug Addiction (EMCDDA) estimated that 18 million Europeans from 15 to 34 years old (which is 15% of that age group) used cannabis in 2018 [6]. In Spain, the estimate was even higher, at 18.3%. The typical Spanish problematic cannabis user (defined as someone using cannabis at least 20 days monthly) is male (80%), under age 35 (70%), and single (70%), with a secondary education (72%) and currently working (49%), while smoking an average of three joints per day [7, 8]. There was, however, a sizeable gap identified during the Spanish general population survey called EDADES (Encuesta Sobre Alcohol y Drogas en España) between the estimated number of problematic cannabis users between 15 and 64 years old and the number in that same age group seeking treatment (6%) [9]. Cannabis users have a risk of addiction that ranges from 10% to 20% and this risk is increased by certain factors, like early-onset consumption, problematic consumption over the preceding 12 months [8], and higher product THC concentrations [10, 11].

The current acceptability of cannabis use as a personal option demands new regulations regarding its consumption and distribution. It also requires developing strategies that help convey to citizens the potential risks of cannabis use (short-term, long-term, and due to heavy use) and offer accessible and effective therapeutic approaches [12].

In Spain, a broad, diversified and readily-accessible public drug treatment network has been developed in recent decades [13]. According to the national health system, its underlying principles and goals focus on universality, free access, equity, and fairness of financing. Still, it should be noted that a high percentage of problematic cannabis users do not seek treatment anywhere (93%). Moreover, there is a lack of approved pharmacological treatments (despite a wide range of off-label treatments for CUD and cannabis withdrawal) and high attrition rates for most of these treatments [14]. Consequently, innovative intervention strategies are needed [9]. Today, young people are very familiar with the use of new technologies in almost all areas of life and the age group most likely to accept and benefit from new technologies used therapeutically [15].

The COVID-19 pandemic has brought a wide variety of unprecedented challenges, many of which appear to be affecting mental health and consumption patterns in cannabis users [16–19]. Therefore, it is essential for healthcare providers to use all the resources and therapies available to help users adjust to the problems caused by the pandemic. Recent meta-analyses [20–22] have assessed how effective internet interventions (OCIs) are at reducing cannabis use. However, these interventions are well known to have low adherence and follow-up rates [23].

The CANreduce intervention is an integrated, online, and self-guided treatment program designed to help cannabis users reduce their cannabis consumption. Developed by the Swiss Research Institute for Public Health and Addictions, it has been certified as safe by the European Union. It is considered a medical device under European Union guidelines 93/42/EWG and 2007/47/EWG. Randomized clinical trial (RCT) results were published in 2015, demonstrating CANreduce to be effective, though beset by an adherence rate that might be improved by creating internet-based applications responsive to all devices (phones, tablets, computers) and adding psychological support [24]. An updated, adherence-focused guidance enhanced version, CANreduce 2.0, has since been developed [25] and found to be effective [26].

For the current study, CANreduce 2.0 (an adherence-focused, guidance-enhanced, web-based self-help tool) [26] was translated into Spanish (CANreduce-SP) and its effectiveness with versus without psychological support compared, in terms of reducing cannabis use among problematic users. Adding psychological support (the option for program users to contact an e-coach to resolve doubts or any concerns they have regarding the program or process) is expected to optimize both adherence to and the effectiveness of the program. Previous studies have identified low demand for this type of support, but better results with similar support options, like chat sessions with a counsellor [24].

Study hypotheses will be tested concerning the main outcome: reduction in the number of days of cannabis use over the prior week, comparing assessments at baseline versus 6-week, 3-month, and 6-month follow-up. A priori study hypotheses are:

The CANreduce-SP program with psychological support (study arm 1) will be more effective than CANreduce-SP with no psychological support (study arm 2) at reducing cannabis use.The CANreduce-SP program with psychological support (study arm 1) will be more effective than treatment as usual (TAU, study arm 3) at reducing cannabis use.The CANreduce-SP program without psychological support (study arm 2) will be more effective than TAU (study arm 3) at reducing cannabis use.Participants in study arm 1 will demonstrate better adherence than participants in study arm 2 over the 6-week intervention.

Secondary cannabis-related outcomes will be tested similarly, and frequently co-occurring mental disorders explored as predictors of adherence and outcomes.

## Methods/design

The Spanish version of the adherence-focused, guidance-enhanced, web-based self-help program CANreduce 2.0 (CANreduce-SP) will be evaluated within a three-arm RCT, in which the effectiveness of CANreduce-SP with psychological support and CANreduce-SP without psychological support will be compared against each other and against treatment-as-usual (TAU) at reducing cannabis use in problematic users. Given that the study will only be partially single-blinded, the two active intervention arms will be neutrally described to subjects assigned to those arms to prevent participants from preferring one over the other. However, participants assigned to TAU will immediately be made aware of their group. As for study personnel, though any who directly provided support to program users cannot feasibly be blinded to subjects’ group assignments, all other study personnel (e.g. those involved in data collection, editing and analysis) will be. Co-occurring mental health symptoms will be screened with the rest of the primary and secondary outcomes during the baseline assessment (*t*_0_) to ensure that all potential participants meet study criteria and are eligible to be randomized and allocated to one of the three study conditions. Further assessments will take place 6 weeks after baseline, which is also the time when participants will have completed the 6-week program (*t*_1_), as well as at 3 months (*t*_2_), and 6 months (*t*_3_) follow-up (Fig. 1). Having 6 months of follow-up will allow us to examine the durability of any changes achieved with either of the two active interventions (study arms 1 and 2). For ethical reasons, we have elected not to ask study participants in the TAU group to wait a full 6 months for their final follow-up. Instead, we will grant them access to the intervention group without psychological support (study arm 2) 18 weeks after baseline—6 weeks after their 3-month evaluation (*t*_2_)—with the intention of assessing any response to the program they might have had at the 6-month follow-up assessment (t_3_). In this way, they will provide the study with a further, cross-over comparison.

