### Measurements

All data will be retrieved online. Sociodemographic data will include subject gender, age, autonomous community, education level, and work status. The primary outcome will be the number of days of cannabis use over the preceding seven days, according to the Time-Line-Follow-Back (TLFB) method [36, 37]. The TLFB is a calendar used in many studies to obtain estimates of the quantity of daily drug use (alcohol, cannabis, cocaine…). It is broadly recommended to be used for outcome evaluation and treatment planning purposes.

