### Data analysis

All analyses will be performed on an intention-to-treat basis and verified by complete case analyses. Imputation procedures will be chosen based on missing data patterns (e.g. using the MICE multiple imputation function in the statistical software package R and between 20 and 40 imputed datasets, depending on the extent of missing data, in accordance with suggestions made by Graham [47]). Moreover, study dropout analysis will be performed comparing participants who completed the follow-up survey against those who did not. Cohen’s *d* will be determined, with the significance threshold for all analyses defined as alpha = .05. The primary outcome—number of days of cannabis use over the preceding 7 days, estimated using the Time-Line-Follow-Back method—will be analysed by means of linear regression models with baseline characteristics and group allocation as predictors. Secondary outcomes will be analysed accordingly.

Since this will be a low-risk intervention, there will be no independent data monitoring committee. Study data will be analysed by the lead and the principal investigator after completion of data acquisition. Planned analyses are described in this section. There will be no formal stopping rules since we do not anticipate problems detrimental to participants. Data collection will be stopped when at least one hundred and fifty participants will be included in each group. The lead investigator and the principal investigator will make the final decision to terminate the data collection.

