### Composition of the coordinating centre and trial steering committee

The steering committee consisting of all lead and principal investigators of the two research centres will have virtual meetings to address goals and progress of the project monthly for 6 months and later when needed. The lead investigator of the present RCT trial was responsible for the study design, prepared the protocol, and will organize weekly virtual or presential meetings with the trial management group. In these meetings, the trial management group will report on problems and progress of ongoing data collection. The trial management group will consist of 2 research assistants (psychologist) responsible for Google Ads review, who will answer to the participants’ emails (general questions or psychological support), sending the SMS reminders and helping participants to fulfil the follow-up questionnaires by phone. The lead investigator together with the principal investigator will decide on trial termination and will write up study results for publication.

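### Data collectors are said to be blinded, but the two assistants who answer arm 1's support e-mails are also assigned the follow-up questionnaires completed by phone

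*Protocol article*

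**What the plan says.** The Methods/design section calls the design one in which "the study will only be partially single-blinded". It sorts staff into two groups. Of the first it says that "any who directly provided support to program users cannot feasibly be blinded to subjects’ group assignments". Of the second it says that "all other study personnel (e.g. those involved in data collection, editing and analysis) will be" blinded. Data collection is thus named as a blinded activity.

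The section on the composition of the coordinating centre describes the staffing: "The trial management group will consist of 2 research assistants (psychologist) responsible for Google Ads review". The same sentence makes these two assistants responsible for answering participants' "emails (general questions or psychological support), sending the SMS reminders and helping participants to fulfil the follow-up questionnaires by phone".

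The Randomization and trial flow section shows that the phone contact is outcome collection. After an unanswered e-mail and two repeats, and a further week, "participants will be contacted by phone and will be offered the option of completing the follow-up questionnaire verbally with an interviewer".

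Under Active study arms, psychological support is confined to arm 1 and is given only when the participant asks for it. The primary outcome is days of cannabis use in the past seven days (Measurements), and the Limitations section says that all measures are self-reported.

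**The concern.** Blinded outcome collection needs the collectors to be people who do not know the arm. Here the only staff named for phone collection are also the only staff named for the unblinded task. An assistant who has exchanged support messages with a participant knows that this participant is in arm 1.

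The consequence may differ by arm. Only in arm 1 can a participant report use to someone who has given them personal feedback. The protocol's own rationale for support, in the Psychological support section, is accountability to a trusted coach. A participant who feels accountable to the caller may under-report days of use. That would favour arm 1 in the comparisons with arm 2 and with treatment as usual (hypotheses 1 and 2). The comparison of arm 2 with treatment as usual (hypothesis 3) is not exposed to this route.

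Also at stake is the accuracy of the trial report, which would claim a safeguard that the staffing plan does not provide.

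**Working it through.** **Consistency check.** The plan states no figure on this point, so the sections are set side by side.

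1. Methods/design: support staff are unblinded; data collectors are blinded. Both hold only if the two groups do not overlap.
2. Coordinating centre: two assistants are named, and support e-mails and phone questionnaires are both in their task list.
3. Randomization and trial flow: the phone contact is an interview that yields follow-up data.
4. Active study arms: support exists in arm 1 only, so knowledge gained by giving it identifies arm 1.
5. No section divides the tasks between the assistants, and none says that callers are kept unaware of the arm.

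The groups in step 1 therefore overlap on the current text, for phone-collected outcomes.

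**Illustration of size.** The documents give none of the four inputs below; all are assumptions.

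- u, share of arm 1 participants who use support: 10% to 30%. The Background reports low demand in previous studies, and Expected principal findings anticipates very few messages.
- f, share of outcomes collected by phone: 30%.
- s, extra under-reporting when speaking to one's own coach: 0.5 to 1.0 day.
- SD of days of use: 1.5 to 2.5 days.

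Two further assumptions: support use and phone completion are independent, and every supported participant who is phoned is phoned by the person who supported them.

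Bias in days = u × f × s; bias in SD units = that value / SD.

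- Low end: 0.10 × 0.30 × 0.5 = 0.015 day; 0.015 / 2.5 = 0.006.
- High end: 0.30 × 0.30 × 1.0 = 0.09 day; 0.09 / 1.5 = 0.06.

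As a share of the d = 0.40 in the Sample size calculation: 0.006 / 0.40 = 1.5% and 0.06 / 0.40 = 15%.

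**Effect on error rate.** With 100 per arm and a two-sided 5% t-test, a pure bias of 0.05 SD (noncentrality 0.05 × √50 = 0.354, 198 degrees of freedom) raises the chance of a significant result under no true effect from 5% to 6.4%. A bias of 0.01 SD raises it to 5.1%.

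**The case against.** The strongest reply is that the task list is collective. It does not say that each assistant does every task, or that a coach phones the people she has coached, and a full protocol may already divide the work. That stands as a limit: the text shows that the claimed blinding is not secured, not that it has failed in practice. It does not remove the conflict, because the article states both halves itself.

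Exposure is also narrow. A participant must have written for support, then left the e-mails unanswered, then accepted an optional call. People who write to a coach may not be typical non-responders. This stands, and it is why the estimate includes support uptake.

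The contrast between arms is not absolute. The assistants also answer general questions, and arm 2 receives the e-coach's videos and automated e-mails. Participants in treatment as usual know their group, so blinding the caller would not remove reporting bias in comparisons with that arm. All of this stands; what is specific to arm 1 is personal feedback from a possible interviewer.

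A reader might infer four stronger points that the documents do not support:

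- **Unblinded analysts.** The Data analysis section says that "Study data will be analysed by the lead and the principal investigator after completion of data acquisition". It does not say that they see arm labels. The weekly meetings are organized by the lead investigator alone, and their stated content is problems and progress of data collection.
- **A bias of 15% to 50% of the planned effect.** Leaving out uptake gives 0.30 × 0.5 / 2.5 = 0.06 to 0.30 × 1.0 / 1.5 = 0.20. That treats every arm 1 participant reached by phone as coached by the caller, contrary to the low uptake that the protocol expects.
- **Phone calls supplying many of the outcomes because 50% attrition is expected.** Attrition counts people who give no outcome; it does not tell us how the others gave theirs.
- **A real conflict with the statement that "All data will be retrieved online".** This can describe the default mode, and a caller could enter answers in the web form. It is a minor wording matter.

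**Conclusion.** The point holds for data collection by phone. On the current text, the staff whom Methods/design says cannot be blinded are those named for completing follow-up questionnaires by phone, and nothing separates the roles or conceals the arm. The result is a risk of differential reporting on the self-reported primary outcome that could favour arm 1. It is not a demonstrated bias.

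Its size cannot be derived from the documents. Under the assumptions shown it is about d = 0.006 to 0.06, at most 15% of the planned effect, and outcomes completed online are not affected. The correction is worth making because it is cheap, it touches the primary outcome, and mode and interviewer cannot reliably be reconstructed later. The trial's validity does not turn on it.

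**What to change.** 1. Assign support e-mails to one of the two existing assistants and follow-up calls to the other. The caller should work from a list without arm and from a fixed script.
2. Record, for each follow-up outcome, the mode (web or phone) and the interviewer.
3. Report a supportive sensitivity analysis of the primary outcome by mode. State that a web-only analysis conditions on response behaviour after randomization, which may differ by arm, so it cannot replace the intention-to-treat analysis.
4. Reconcile Methods/design, Randomization and trial flow, and the coordinating-centre section, so that they say who makes the calls and whether that person knows the arm. If the roles cannot be split, withdraw the claim of blinded data collection for outcomes collected by phone.

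Cost: no extra staff. The assistants lose some flexibility to cover for each other, and the trial gains the mode and interviewer record and one extra analysis.
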